### Sample size considerations

In order to detect a 5% reduction at endline in the proportion of adults aged 35 years and above who are at moderate or high risk of CVD [38,39] in the intervention population versus no change in the control population (assuming both populations have similar start prevalence at 25%), we need 2,927 respondents in both intervention and control sites, using an alpha of 0.05 and power (1-beta) of 0.90. Taking into account a non-response rate of 10%, we will approach 3,220 individuals per cross-sectional study—that is, 1,610 per site at baseline and endline surveys, respectively.

The sampling frame will be based on the most recently updated NUHDSS database. This database contains details of about 72,000 individuals including names, locations, gender, dates of birth and residential status in both slums. In the control site, we will use computer randomization (STATA® statistical software) to select the 1,610 individuals aged 35 years and older per site for each cross-sectional survey.

In the intervention site, the same computer randomization process will be followed. However, unlike the control site, the 1,610 individuals to be included in the cross-sectional survey analysis will be collected retrospectively. In other words, the intervention package will be delivered to all adults aged 35 years or older in the intervention site—that is, 6,780 individuals according to the DSS database (as at 15 June 2012).

At the clinic level, we calculated that in order to detect a 10 mmHg reduction in blood pressure (at 20 mmHg standard deviation, alpha of 0.05 and 1-β on 0.9), about 44 participants are needed. However, it is projected that approximately 1,350 participants (out of 6780) will be referred from the door-to-door visit. This number is derived from a 20% prevalence of hypertension among adults aged 35 years and older in the study area [27]. We estimate that roughly half of these 1,350 participants, being 675, will continue visiting the clinic for treatment. Hence, this number of people is more than sufficient for the analysis of our main primary outcome at the clinic level.

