### Analysis

Due to the fact that the slums are part of a large demographic surveillance site and therefore not randomized, we will use the double-difference method [40] to evaluate the primary outcomes in the intervention versus control sites. In this approach, Impact = (Y_p(t>0)_ – Y_p(t=0)_) – (Yc_(t>0)_ – Yc_(t=0)_) where Y_p_ is the primary outcome in the intervention group and Y_c_ is the outcome in the control group. For the double-difference method to work, it is essential that there are at least two pre-intervention data points. In addition, having many preintervention data points allows for the detection of shifts or interruptions in trends (if any) after the introduction of an intervention. A cross-sectional study conducted in the NUHDSS from 2008–2009 provides one time point of pre-intervention data on CVD risk in the intervention and control slums [27]. Note that cardiovascular risk reduction will be calculated by entering the outcomes in a non-laboratory-based CVD risk assessment chart [33]. Regression analyses will also be performed to investigate the association of each risk factor with the main outcomes such as blood pressure. Specifically, multivariate analyses will be used to adjust for known or perceived confounding variables while comparing outcomes between intervention and control sites. Prior to this, descriptive statistics will be applied to compare characteristics of the intervention and control sites. For behavioral risk factor analysis, we will use an interpretive descriptive approach with matrix comparisons between groups (such as sex, age group and site).

Cost-effectiveness analysis will be conducted according to the WHO framework for cost-effectiveness analysis [41]. This framework will consider intervention effectiveness data based on changes in blood pressure and overall predicted cardiovascular risk at the population level, as well as cost data on the intervention. The overall cost-effectiveness of the intervention package will be calculated in terms of DALYs averted per US dollar.

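### The 90% power for primary outcome 1 belongs to a single two-sample comparison; for the planned double difference over four samples it is about 61%

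*Protocol article*

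**What the plan says.** Sample size considerations sets the target for the first population-level outcome: "In order to detect a 5% reduction at endline in the proportion of adults aged 35 years and above" who are at moderate or high cardiovascular risk, "in the intervention population versus no change in the control population", with both sites starting at 25%. From this it concludes that "we need 2,927 respondents in both intervention and control sites, using an alpha of 0.05 and power (1-beta) of 0.90". It continues: "Taking into account a non-response rate of 10%, we will approach 3,220 individuals per cross-sectional study", divided as "1,610 per site at baseline and endline surveys, respectively".

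Primary outcomes defines outcome 1 as the difference between the slums in the change of a proportion. Data management describes two cross-sectional surveys 12 months apart. The Analysis section says "we will use the double-difference method [40] to evaluate the primary outcomes in the intervention versus control sites" and writes the estimator out as the change in the intervention site minus the change in the control site.

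**The concern.** The sample size formula and the estimator do not match. The calculation uses two proportions; the estimator uses four, each from its own survey sample of about the same size. Assuming that both sites start at 25% makes the expected baseline difference zero. It does not remove the sampling error of the two baseline estimates that the double difference subtracts. Leaving that error out roughly halves the variance.

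The outcome is the first listed primary outcome, and population-level risk change also feeds the cost-effectiveness analysis. A reader told that power is 90% expects a true 5-point effect to be missed one time in ten. With power near 61% it would be missed about four times in ten, and a non-significant result could be taken as stronger evidence against the package than it is.

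**Working it through.** **Inputs** (all from Sample size considerations): intervention site 25% falling to 20%; control site 25% at both surveys; alpha 0.05; power 0.90; 2,927 respondents per survey for both sites; 1,610 approached per site per survey; 10% non-response. Sidedness is not stated.

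**Step 1: reproduce 2,927.** The pooled two-proportion formula, two-sided, has mean proportion 0.225:

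n = [1.96 × √(2 × 0.225 × 0.775) + 1.2816 × √(0.25 × 0.75 + 0.20 × 0.80)]² / 0.05² = 1,463.7 per group, or 2,927.4 in total.

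This is the stated figure. A one-sided test gives 2,386 and does not match. Reading 2,927 as a per-site number conflicts with 3,220 approached per survey. The figure therefore covers one contrast between two samples, whether that is intervention against control at endline or before against after within one site.

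**Step 2: respondents expected.** 3,220 is 2,927 × 1.10. At 10% non-response, 3,220 × 0.90 = 2,898 respond, which is 1,449 per site per survey.

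**Step 3: power of the double difference.** With four independent samples of n each:

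Variance = (3 × 0.25 × 0.75 + 0.20 × 0.80) / n = 0.7225 / n

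Power = Φ(0.05 / SE − 1.96)

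| Respondents per site per survey | SE (points) | 0.05 / SE | Power, double difference | Power, endline contrast only |
|---|---|---|---|---|
| 1,449 (1,610 less 10%) | 2.23 | 2.24 | 61.0% | 89.7% |
| 1,463.5 (2,927 / 2) | 2.22 | 2.25 | 61.4% | 90.0% |
| 1,610 (all respond) | 2.12 | 2.36 | 65.6% | 92.5% |

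Simulation of independent binomial samples gave 61.0% at 1,449 and 61.5% at 1,464. The last two columns differ only by the baseline variance terms, so these account for the whole gap.

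**Step 4: what the planned size does support.** At 90% power the detectable difference is about (1.96 + 1.2816) × 2.22 = 7.2 points. It is about 7.1 if the endline variance is recomputed at the larger effect. For 5 points at 90% power, n = 3.2415² × 0.7225 / 0.0025 ≈ 3,037 per site per survey, about twice the plan. The 95% half-width is 1.96 × 2.23 ≈ 4.4 points.

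**Step 5: sensitivity to independence.** Two draws of 1,610 from the 6,780 eligible adults in the intervention site share about 1,610 / 6,780 = 24% of persons by chance. The size of the control frame is not given, so a similar fraction is assumed there. With an assumed within-person correlation of 0.5 to 0.8, the average baseline–endline correlation is 0.24 × 0.5 = 0.12 to 0.24 × 0.8 = 0.19. Power is then about 66–71%. Using a finite-population correction instead (1 − 1,449 / 6,780 = 0.79 on the variance, same frame assumption) gives about 71–72%. These are two treatments of the same feature, a sample that is a sizeable part of its frame, so the gains should not be added. An average correlation of about 0.5 would be needed to reach 89%.

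**The case against.** The best defence is that 61% is a floor. Independence is not exact, since some persons will be sampled twice. The intervention baseline could in principle use everyone screened, which would give about 71%, although the article says that 1,610 are analysed. The Analysis section also already plans multivariable adjustment, which may recover some precision. All of this stands, and it is why a range is proper. None of it restores 90%: the article states no repeat measurement of the same people and quantifies no precision gain. In the other direction, one site per arm and any village or household clustering are not charged for.

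A reader might draw stronger conclusions, which the documents do not support:

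- **That a null result could never exclude a 5-point fall.** With a half-width of about 4.4 points, an estimated reduction below about 5.0 − 4.4 = 0.6 points would exclude it. The answer depends on the interval.
- **That the effect must be small because "roughly half of these 1,350 participants, being 675, will continue visiting the clinic for treatment".** This assumes no effect outside clinic care, whereas the package includes awareness campaigns and counselling for all eligible consenting adults. Any power figure built on the 675 also needs a response fraction that the article does not give.
- **That power for mean systolic pressure follows from 10 mmHg and an SD of 20.** Those are the clinic-level target and SD. The stated 44 participants matches a one-sample or paired calculation, so 10 mmHg is not a population forecast and 20 is not shown to be a cross-sectional SD.
- **That the number approached should be raised to 2,927 / 0.90, about 3,252.** This re-inflates a figure that does not fit the estimator, and shortfall in respondents moves power only from 61.4% to 61.0%.

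**Conclusion.** The point holds. The 90% is correct for one contrast of 25% with 20% and wrong for the double difference the article plans. Under four independent samples, two-sided alpha 0.05, the article's own 25% and 20%, and no design effect, power for 5 points is about 61% (61.0% at the expected 1,449 respondents per site per survey). Chance overlap or a finite-population correction, under the assumptions stated, brings it to about 66–72%; clustering would reduce it. The conclusion is limited to the stated power for outcome 1. It does not show that the study cannot inform on a 5-point effect, and it says nothing about power for systolic pressure or the clinic-level outcome.

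**What to change.** Keep enrolment as planned and restate Sample size considerations for the double-difference estimator:

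- Say that 3,220 approached per survey yields about 2,898 respondents at 10% non-response, or 1,449 per site.
- Give power of about 61% for a 5-point difference in change with independent samples and no design effect, and up to about 70% under overlap assumptions that are written down.
- Give a detectable difference of about 7 points at 90% power.
- Add that the population-level result will be interpreted from its confidence interval (expected half-width about 4.4 points), and that a non-significant result alone is not evidence against a 5-point effect.

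The cost is a rewritten paragraph and a less favourable power statement. No additional participants or measurements are needed.

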#### (1) Raising awareness and (2) improving access to screening

The first two components of the intervention package include door-to-door household visits by community health workers (CHWs) to raise awareness about CVD risk and to conduct screening of each eligible adult aged 35 years and above in the intervention slum in order to determine their individual CVD risk profile. CHWs are typically community-based volunteers who have an interest in community health. They are usually well known by the community and most have received some form of basic training in community health activities such as peer health education for HIV/AIDS prevention. The SCALE UP study will recruit CHWs to represent each of the eight villages in the intervention slum. These CHWs will then be trained and equipped to perform the door-to-door visits and screening exercise in their respective villages in the intervention slum.

Two weeks prior to the commencement of the screening exercise, there will be public awareness campaigns organized by the CHWs in each village of the intervention slum. This awareness campaigns will take place at community gatherings (known locally as *barazaas*). At these *barazaas*, CHWs together with village leaders will inform the audience about the burden of CVD in the community and the need to participate in the door-to-door screening. Additionally, CHWs will visit religious gatherings, usually held at local churches and mosques, to provide the same information. Such gatherings are usually well attended by respected members of the community who will then pass the information on to others. Finally, radio jingles announcing the door-to-door screening will be aired daily on the local radio station (Korogocho FM) over a 2-week period from the start of the intervention.

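### The Korogocho baseline cell is limited to a random 1,610 although every eligible adult there is screened and measured, which costs precision in the double difference for no gain in validity

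*Protocol article*

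**What the plan says.** All references are to the protocol article.

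- **Sample size considerations.** The plan needs 2,927 respondents over the two sites and approaches 1,610 per site in each survey. The control sample is drawn by computer from the surveillance database. For the intervention site the text says that, "unlike the control site, the 1,610 individuals to be included in the cross-sectional survey analysis will be collected retrospectively". The reason offered is that "the intervention package will be delivered to all adults aged 35 years or older in the intervention site", which is 6,780 people on the database.
- **Raising awareness and improving access to screening.** Community health workers (CHWs) make household visits "to conduct screening of each eligible adult aged 35 years and above in the intervention slum in order to determine their individual CVD risk profile". They are trained to assess lifestyle risk and to take blood pressure and anthropometry, and they make at most two contact attempts.
- **Data management.** CHWs also take the physical and clinical measurements for the survey in the intervention site. Field interviewers collect the demographic, socioeconomic and behavioural interview data in both sites.
- **Primary outcomes.** Outcomes 1 and 2 are differences in change between the two slums.
- **Analysis.** The text says "we will use the double-difference method [40] to evaluate the primary outcomes in the intervention versus control sites".

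No reason is given for holding the Korogocho baseline to the size of the control sample.

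**The concern.** The 1,610 comes from an equal-allocation comparison of two proportions. In the control slum it sets how many people to measure. At baseline in Korogocho it does something else: it limits how many of the people measured enter the analysis.

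The double difference is built from four cell means, and its variance is the sum of the four cell variances. Nothing in it requires equal cells. A random subset of the screened adults has the same expected value as the full screened set. It has the same measurers, the same contact rule and the same selection by who was at home. Subsetting therefore makes Korogocho no more comparable with Viwandani; it only enlarges one of the four variance terms. What is at stake is the width of the interval, and so the power, for the change in the proportion at risk and the change in mean systolic pressure.

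**Working it through.** **1. Reproducing the plan's figure.** The inputs, all from Sample size considerations, are 25% against 20%, 90% power and alpha 0.05 (two-sided assumed, since sidedness is not stated). The pooled formula per site is

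n = [1.960 × √(2 × 0.225 × 0.775) + 1.2816 × √(0.25 × 0.75 + 0.20 × 0.80)]² / 0.05² = (1.1575 + 0.7555)² / 0.0025 ≈ 1,464.

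That is 2,927 over both sites before rounding up, which is the stated figure. 2,927 × 1.10 = 3,220, or 1,610 per site. A one-sided test would give 2,386, so two-sided is the plan's basis. The formula compares endline proportions only. It contains no baseline sampling error, so it cannot show whether a baseline cell of 1,610 is adequate for a double difference.

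**2. The double difference as planned.** Respondents per cell: 1,610 × 0.9 = 1,449. The cell variances are 0.25 × 0.75 = 0.1875 for three cells and 0.20 × 0.80 = 0.16 for the intervention endline.

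SE = √[(3 × 0.1875 + 0.16) / 1,449] = √(0.7225 / 1,449) = 0.0223

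Power = Φ(0.05 / 0.0223 − 1.96) = 61.0%

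The Korogocho baseline contributes 0.1875 / 0.7225 = 26% of this variance, so 26% is the most that any enlargement of that cell could remove.

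**3. Using the screened records.** The other three cells stay at 1,449, so

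SE = √[0.1875 / n + (0.16 + 2 × 0.1875) / 1,449].

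The 6,780 is a frame count before exclusions, refusals and failed contacts, so I show a range.

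| Korogocho baseline records, n | SE (points) | Variance reduction | Power |
|---|---|---|---|
| 1,449 (as planned) | 2.23 | – | 61.0% |
| 4,000 | 2.04 | 17% | 68.8% |
| 5,000 | 2.02 | 18% | 69.8% |
| 6,102 (0.9 × 6,780) | 2.00 | 20% | 70.5% |

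With 1,464 per cell in place of 1,449, the last comparison is 61.4% to 71.0%.

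**4. Sensitivity to clustering (assumed design effects, n = 6,102).**
- Design effect 1.5: 44.8% to 53.2%, a gain of 8.5 points.
- Design effect 2: 35.3% to 42.4%, a gain of 7.1 points.

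Positive within-person correlation among people in both waves would push the gain slightly the other way (10.2 to 11.1 points for an assumed correlation of 0.3 to 0.7). I do not rely on that.

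**5. Mean systolic pressure.** The only SD in the article is 20 mmHg, in the clinic-level calculation, so using it for the population is an assumption.

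As planned: SE = 20 × √(4 / 1,449) = 1.05 mmHg.

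With n = 6,102: SE = 20 × √(1 / 6,102 + 3 / 1,449) = 0.95 mmHg. With n = 4,000 it is 0.96 mmHg.

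Multiplying by 3.24, the difference detectable with 90% power falls from 3.4 to 3.1 mmHg. The SE shrinks by 8-10% whatever the SD.

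**The case against.** **The 25% may not belong to outcome 1 as worded.** This stands. The abstract and Sample size considerations speak of moderate or high risk, while Primary outcomes defines outcome 1 as high risk only and gives no prevalence. Purely as an illustration, suppose a 10% prevalence in both slums. A fall to 5% would take power from about 92% to 97%, and a fall to 7.5% from about 37% to 45%. The direction survives; the size in points does not carry over.

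**A reader might infer that about 4,650 records are lost** (0.9 × (6,780 − 1,610) = 4,653), with a cost of 9-10 points of power. That is the top of the range, because it takes 90% of the frame as measured. It also overstates the text, which only limits who enters the survey analysis. The other screening records still serve referral, and uptake after referral is a secondary outcome.

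**A reader might also infer that the remaining records are identical to the survey records.** The article does not settle this. CHWs take blood pressure and anthropometry and assess lifestyle risk on everyone they screen. It is not stated that all of them receive the interviewer-administered survey of about 30 minutes. A covariate-adjusted model that uses those items may be confined to the 1,610. The CHWs' glucose test is limited to a subgroup of those over 55. As far as screening data go, though, that rule falls equally on the 1,610 and the rest, so it is no reason to subset.

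**The choice causes no bias and the gain is modest.** Both are true. This is a point of efficiency, not of validity.

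**Conclusion.** The point holds as a matter of efficiency. Limiting the Korogocho baseline cell to 1,610 costs precision on the two population-level primary outcomes, and the article states nothing that is gained by it. On the moderate-or-high basis, with the plan's 25% and 5 points, 1,449 in each other cell, independent individuals and two-sided alpha of 0.05, admitting 4,000 to 6,102 baseline records lowers the variance by about 17-20% and raises power from about 61% to 69-71%. Over plausible coverage and clustering the gain is about 7-10 points. For high risk alone it is unknown. For mean systolic pressure the SE falls from 1.05 to about 0.95 mmHg if the SD is 20 mmHg.

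It would be wrong to conclude that this brings the study back to its stated power. Under the same assumptions, 90% power for the double difference needs about 3,037 per cell: (1.960 + 1.2816)² × 0.7225 / 0.0025. Nor does a larger baseline in one slum help with having a single slum per arm, where a difference in local trend cannot be told apart from the intervention effect.

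**What to change.** In Sample size considerations, replace the retrospective selection at the intervention baseline with a sentence such as: *All eligible, consenting adults screened at baseline in the intervention site who have the measurements needed for the risk score and systolic blood pressure enter the baseline cell of the double-difference analysis.*

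Alongside it:

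- keep the random 1,610 for the control baseline and for both endline surveys;
- use standard errors that allow for people who appear in both waves;
- keep the 1,610 subset as a sensitivity analysis, and for any adjusted model that needs items collected only in the interviewer-administered survey;
- state which risk category the 25% refers to, so that the gain can be read against primary outcome 1.

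The cost is a sentence or two of text, the cleaning of more electronic screening records, and unequal cells in the analysis. For the screening measurements, no extra participants, visits or tests are needed.

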### Analysis

Due to the fact that the slums are part of a large demographic surveillance site and therefore not randomized, we will use the double-difference method [40] to evaluate the primary outcomes in the intervention versus control sites. In this approach, Impact = (Y_p(t>0)_ – Y_p(t=0)_) – (Yc_(t>0)_ – Yc_(t=0)_) where Y_p_ is the primary outcome in the intervention group and Y_c_ is the outcome in the control group. For the double-difference method to work, it is essential that there are at least two pre-intervention data points. In addition, having many preintervention data points allows for the detection of shifts or interruptions in trends (if any) after the introduction of an intervention. A cross-sectional study conducted in the NUHDSS from 2008–2009 provides one time point of pre-intervention data on CVD risk in the intervention and control slums [27]. Note that cardiovascular risk reduction will be calculated by entering the outcomes in a non-laboratory-based CVD risk assessment chart [33]. Regression analyses will also be performed to investigate the association of each risk factor with the main outcomes such as blood pressure. Specifically, multivariate analyses will be used to adjust for known or perceived confounding variables while comparing outcomes between intervention and control sites. Prior to this, descriptive statistics will be applied to compare characteristics of the intervention and control sites. For behavioral risk factor analysis, we will use an interpretive descriptive approach with matrix comparisons between groups (such as sex, age group and site).

Cost-effectiveness analysis will be conducted according to the WHO framework for cost-effectiveness analysis [41]. This framework will consider intervention effectiveness data based on changes in blood pressure and overall predicted cardiovascular risk at the population level, as well as cost data on the intervention. The overall cost-effectiveness of the intervention package will be calculated in terms of DALYs averted per US dollar.

Intervention cost will be estimated using a micro-costing approach where feasible. Micro-costing is a process of systematically identifying and measuring resource utilization using a process tracking system and interviews with the local program team [42]. According to the Panel on Cost-Effectiveness in Health and Medicine, the theory and process of valuing costs through a micro-costing methodology rest on a three-step approach: identification, measurement and valuation of resources used [43]. For other non-specific costs, gross costing methods will be considered. Once resource utilization has been measured, the component-specific costs of the intervention can be computed by multiplying the quantity of each type of resource consumed by unit costs. The component-specific costs can be summed up to get the total costs of the intervention [42]. Finally, the outcome of this analysis will be the average cost for CVD risk reduction per participant per year. Data on costs and timings will be collected from the preparation of the intervention until the end of the intervention period. A yearly discount rate of 3% will be used for long-term modeling and projections [44]. Estimations will be extended to project the cost-effectiveness of the intervention package were it implemented on a national scale.

Finally, in order to determine the scalability and feasibility of the intervention package, a comprehensive process evaluation will be conducted involving analysis of operational data as well as qualitative sub-studies with beneficiaries and other relevant stakeholders such as local policy makers.

Additionally, since the package is to be implemented in a private health sector setting, it will be important to examine essential aspects of the intervention package that are needed to translate the package to the public sector.

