### Intervention community

Korogocho slum, which has eight villages, each with between 3,000–5,000 residents, will be the intervention site. This slum has one centrally located private health facility with a reliable track record of providing primary health services. This facility is known as *Provide International Clinic*. It is well known in the slum and, although most patients still make out-of-pocket payments for services received, the clinic offers non-profit services at highly subsidized (through donor funding) costs to residents. There are no physicians or medical officers present at this clinic. Nurses and clinical officers (health personnel with a diploma in clinical medicine) provide consultations. However, the facility does not typically provide primary preventive services for CVD such as screening and treatment of hypertension. The location of this clinic and the absence of primary preventive services for CVD guided our choice of intervention site.

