### Control community

Viwandani slum will be the control site. There are seven villages in Viwandani with approximately 2,000–4,000 residents each. Unlike Korogocho, Viwandani does not have a centrally located health facility. The main health facility serving Viwandani is located on the outskirts of the slum. This facility is publicly owned and represents the usual standard of care for CVD that is available to underserved slum communities in Nairobi, thus making Viwandani the appropriate ‘control’ site in comparison with Korogocho. The clinic in Viwandani operates a weekly CVD clinic where approximately 30 patients with uncomplicated hypertension and/or diabetes from Viwandani slums are seen on each clinic day. Like the facility in Korogocho, the Viwandani clinic is also run by nurses and clinical officers.

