### Data management

To measure the health effect of the whole intervention package at the population level, there will be two cross-sectional surveys (before and after, 12 months apart). Data will be collected on demographic and socioeconomic variables, behavioral risk factors such as tobacco and alcohol use, anthropometric measurements such as height and weight, and clinical measurements such as blood pressure and random blood glucose. Four cadres of field staff will be involved in data collection. These include field interviewers, CHWs, field assistants and supervisors.

Field interviewers will be trained by the SCALE UP study investigators to collect the demographic, socioeconomic and behavioral risk factor data using structured interviews during the cross-sectional surveys in both the intervention and control sites. In the intervention site, the anthropometric and clinical measurement will be performed by CHWs. In the control site, however, measurements will be performed by trained field assistants rather than CHWs. This is because CHWs are considered to be part of the intervention. Each interview is estimated to last approximately 30 min, followed by the physical and clinical measurements. The field staff will be instructed to follow standard procedures for all measurements as outlined in the WHO STEPS manual [37]. Specifically, while taking the blood pressure, field staff will be required to ensure that the respondent remains seated for about 5 min, with no talking, holding the monitoring device on the upper arm and holding it at heart level against his/her chest. The blood pressure will be measured three times, using the left arm. To minimize observer bias, validated digital equipment will be used, the OMRON M6® (Digital Automatic Blood Pressure Monitor). Note that referral of participants for further management will be based on the average of the three blood pressure measurements (systolic ≥140 and/or diastolic ≥90 mmHg).

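### Two pre-intervention points are called essential and are available, but Impact uses only the baseline and no step checks whether the two slums were already diverging

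*Protocol article*

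**What the plan says.** The Analysis section explains the choice of the double-difference method by noting that "the slums are part of a large demographic surveillance site and therefore not randomized". Impact is defined as the change from t=0 to t>0 in the intervention slum minus the same change in the control slum, so one pre-intervention value per site enters. The section then states a condition: "For the double-difference method to work, it is essential that there are at least two pre-intervention data points". It adds that several earlier points help to detect shifts in trend, and names the source: "A cross-sectional study conducted in the NUHDSS from 2008–2009 provides one time point of pre-intervention data on CVD risk" in both slums. No later sentence says how that survey enters the estimate, a test or a model. The planned multivariate adjustment is for known or perceived confounders.

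Under Data management, the study runs two cross-sectional surveys of its own, one before and one after, 12 months apart.

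The sites differ in the service that the intervention supplies. Under Intervention community: "the facility does not typically provide primary preventive services for CVD such as screening and treatment of hypertension". That absence, together with the clinic's location, guided the choice of Korogocho. Under Control community: "The clinic in Viwandani operates a weekly CVD clinic where approximately 30 patients with uncomplicated hypertension and/or diabetes" from that slum are seen on each clinic day.

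**The concern.** A double difference removes fixed differences in level between two sites. It does not remove a difference in how the sites would have changed without the intervention. An earlier pre-intervention point is useful because it lets the reader see whether the sites moved together beforehand. The plan says that such a point is essential and has one, but as written the Impact estimate would be the same if the 2008–2009 survey did not exist.

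The assumption of common trends needs checking here because there is one slum per arm, allocation was not random, and the choice of site was tied to the local supply of CVD care. A divergence already under way before inclusion began in August 2012 would be reported as an effect of the package. It would also carry into the cost-effectiveness result, which draws on population-level changes in blood pressure and predicted risk, and into the projection to national scale. The limitations in the Discussion cover generalisability and the inseparable components of the package, but not drift.

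**Working it through.** **1. Required, available and used.** Pre-intervention points required: at least two. Available: two (2008–2009 survey and study baseline). Used in Impact: one per site. Comparisons of the sites' pre-intervention changes: none stated.

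**2. What drift does to Impact.** Let Korogocho change by a + θ, where θ is the intervention effect and a is the change it would have had anyway. Let Viwandani change by b. Then the expected value of Impact is (a + θ) − b = θ + d, with d = a − b. The bias equals d in full. With one site per arm, the four site-by-survey means are used up by site, survey and their interaction. They cannot separate θ from d, and they leave nothing from which to estimate site-by-period variance.

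**3. The plan's own sample size.** Inputs from Sample size considerations: 25% versus 20%, alpha 0.05 (taken as two-sided), power 0.90. With the pooled-variance formula, n per group = [1.96 × sqrt(2 × 0.225 × 0.775) + 1.2816 × sqrt(0.25 × 0.75 + 0.20 × 0.80)]² / 0.05² = 1,464 rounded up, or 2,928 in total, against 2,927 stated. The figure reproduces as a single two-group comparison of independent individuals. It carries no site-by-time component, and it assumes no change in the control site.

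**4. Sampling error of Impact with no effect.** Assumed responders per cell: 1,610 × 0.90 = 1,449. Assumed prevalence: 25% in all four cells. SE = sqrt(4 × 0.25 × 0.75 / 1,449) = 0.02275, or 2.28 points. The 95% half-width is 1.96 × 2.275 = 4.5 points.

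**5. Illustration with random drift.** Let d have mean 0 and SD τ (assumed; the documents give no value). For a nominal 5% test that uses the SE from step 4 alone, type I error = 2 × [1 − Φ(1.96 × SE / sqrt(SE² + τ²))].

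| SD of the between-slum difference in 12-month change | Type I error |
|---|---|
| 1 point | 7.3% |
| 2 points | 14.1% |
| 3 points | 23.6% |

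If the same SDs are instead assigned to each slum's own change, SE² + τ² becomes SE² + 2τ² and the results are 9.6%, 22% and 35%. The table uses the milder definition.

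**6. Illustration with fixed drift.** If d is a fixed 1, 2, 3 or 5 points and there is no effect, Impact is significant with probability Φ(−1.96 + d/SE) + Φ(−1.96 − d/SE) = 7%, 14%, 26% or 59%. The last case is a drift as large as the 5-point target.

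**7. What the 2008–2009 point can deliver.** If its cells were as large as the study's (assumed), the placebo double difference has the same SE of 2.28 points, and power against a 5-point difference is Φ(5/2.275 − 1.96) = 59%. Over an assumed gap of 3 to 4 years, 5 points corresponds to 5/3 = 1.67 or 5/4 = 1.25 points per 12 months. Subtracting the prior slope scaled to 12 months multiplies the variance of Impact by [1 + (1 + 1/g)² + (1/g)²] / 2, where g is the gap in years. This gives 1.44 at g = 3 and 1.31 at g = 4.

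**The case against.** The strongest reply is that the plan meets its own condition. Soon after stating it, the Analysis section names the 2008–2009 survey, and with the baseline that makes two points. The formula is the basic definition of a double difference rather than a full model, and a condensed article may leave modelling detail to a fuller document. The first part stands: a reader might infer that only one pre-intervention point exists, and that would be wrong. The rest does not remove the problem. The article calls the second point a condition of validity and then fixes an estimator that leaves it out.

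A second reply is that Viwandani's weekly clinic is a difference in level, which the method removes, and that Setting describes the slums as socio-demographically similar. Both points are fair. Nothing in the documents shows that the trends did diverge. But similar levels do not establish similar trends, and a site choice tied to service supply is a reason to look.

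Two stronger readings are tempting but unsupported. One is that the trial's confidence intervals will reflect person-level sampling error only. The article states no interval method, so this is an inference from the design and not something the plan says. The other is that the sample size needs a village design effect, or that village-clustered intervals would cure the problem. Individuals are drawn directly from the surveillance database, villages are neither sampled nor assigned, and the documents give no intraclass correlation. Drift shared by a whole slum would not show in differences between its villages.

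**Conclusion.** The point holds in limited form. The plan names the data that its own validity condition calls for but gives them no role, so differential drift between the two slums passes untested and in full into Impact. That follows from the formula and from having one slum per arm, and needs no assumed figure.

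The size of the problem is unknown. The type I errors of about 7%, 14% and 24% are illustrations. They rest on 1,449 responders per cell, 25% prevalence, assumed SDs of 1 to 3 points and a test using person-level sampling error alone. They are not estimates of this trial's actual error rate. A single pre-period contrast is also a modest check and cannot prove that trends were parallel. This is worth changing because the check uses data the plan already cites. It does not show that the double-difference approach should be abandoned.

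**What to change.** In the Analysis section, give the 2008–2009 survey a stated role:

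- Restrict it to age 35 and above and to the study's exclusions, where its variables allow.
- Compute the placebo double difference from 2008–2009 to baseline, with its confidence interval, and report it beside Impact for the CVD risk proportion and for mean systolic blood pressure.
- Add a sensitivity analysis in which Impact is corrected for the prior differential trend scaled to 12 months.
- State that with one slum per arm the intervals do not cover site-level drift, and limit the conclusion accordingly.

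The cost is extra analysis and a check that the 2008–2009 instruments and measurements are comparable with the study's own. The trend-corrected estimate has a wider interval (variance about 1.3 to 1.4 times larger under the assumptions in step 7) and relies on the earlier trend continuing in a straight line. The placebo contrast has limited power, so a small value should be reported as reassuring at most. No new data collection is needed.
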